# Efficacy of acupuncture on upper limb dysfunction after stroke: a randomized controlled trial protocol with surface electromyography evaluation

**DOI:** 10.3389/fmed.2025.1615762

**Published:** 2025-07-10

**Keywords:** acupuncture, upper limb dysfunction, randomized controlled trial, stroke, neuromuscular effect

## Abstract

**Background:**

Upper extremity functional reconstruction remains a major clinical challenge in post-stroke neurorehabilitation. Acupuncture has unique advantages as a complementary alternative therapy. Thus, in this study, we aim to compare sham acupuncture to reveal the efficacy and safety of acupuncture in the treatment of upper limb dysfunction post-stroke with surface electromyography (sEMG), a validated objective assessment tool, and a subjective index.

**Methods:**

In this prospective, principal-investigator-blinded randomized controlled trial, 74 patients who meet the inclusion criteria are randomly assigned to the acupuncture and sham acupuncture groups in a 1:1 ratio using a central randomization system. The patients receive the same routine basic treatment. The core acupoints selected in the acupuncture group are GV20 (Bai hui), DU14 (Da zhui), and LI11 (Qu chi). Six non-meridian acupuncture points are selected for the sham acupuncture group. The treatment cycle lasts for 4 weeks, five times per week, for 20 treatments. The Fugl–Meyer Upper Limb Assessment scale score is used as the main outcome. Secondary outcomes include the Motor Status Scale, Action Research Arm Test, Motor Assessment Scale, Self-rating Anxiety Scale, and Self-rating Depression Scale scores. Simultaneously using sEMG as an auxiliary efficacy indicator.

**Conclusion:**

This study assesses the effectiveness and safety of acupuncture for post-stroke upper limb impairment in multiple aspects and elucidates the underlying neuromuscular effect mechanism of acupuncture to provide clinical evidence.

**Registration:**

International Traditional Medicine Clinical Trials Registry. Registration No. ITMCTR2025000228. November 27, 2024. The study was approved by the Ethics Committee of Guangzhou University of Traditional Chinese Medicine, Shenzhen Hospital (Futian), Ethics. No. GZYLL (KY)-2024–045-01. November 13, 2024.

## Introduction

1

Ischemic stroke accounts for approximately 60–80% of acute cerebrovascular diseases (1) and is the second leading cause of death and disability worldwide (2). Approximately 55–75% of stroke survivors experience varying degrees of limb dysfunction, with more than 80% affecting the upper limbs (3). Upper limb dysfunction post-stroke is classified as central paralysis, characterized by loss of motor control, including reduced muscle strength and coordination. It is also accompanied by peripheral nerve symptoms such as pain, fine motor dysfunction, and hypoesthesia (4), significantly impacting patients’ quality of life and physical and mental health. How to effectively treat upper limb dysfunction after stroke has become a major clinical challenge in the field of neurorehabilitation (5). The 2021 guidelines from the American Heart Association (AHA/ASA) recommend mandatory exercise therapy (CIMT), task-oriented training, and high-intensity repetitive exercises as first-line treatments for upper limb dysfunction post-stroke (6). However, the effectiveness of these therapies depends on the patient’s voluntary motor ability, and due to a low cost-effectiveness ratio, patient adherence faces significant challenges (7). Furthermore, although therapies such as mirror therapy, occupational therapy, transcranial magnetic stimulation, and upper limb rehabilitation robots are also widely used in clinical practice, their treatment costs are high, and long-term efficacy evidence remains insufficient (8). Therefore, seeking complementary and alternative therapies to facilitate patients’ recovery is essential (9).

Acupuncture is widely recognized and accepted as a complementary and alternative therapy. It involves inserting fine needles into specific acupoints on the skin to achieve “Deqi” and treat diseases. Acupuncture has the unique advantages of good efficacy, ease of operation, and high safety, which have contributed to its increasing influence around the world. According to the World Health Organization (WHO), 11 countries have recognized the clinical efficacy of acupuncture for upper limb dysfunction (10). Moreover, multiple clinical studies have shown that acupuncture treatment has a significant positive effect on upper limb dysfunction after stroke. Compared with rehabilitation therapy alone, acupuncture may enhance upper limb function through potential multi-target neuromodulation mechanisms (11). Furthermore, combining acupuncture with rehabilitation exercises has a synergistic effect, and preliminary research indicates that it can significantly enhance the recovery of muscle spasms, limb movement, and neurological function (12). However, in the existing research on acupuncture treatment for upper limb function after stroke, outcome assessments often rely excessively on subjective scales, leading to questions about the level of evidence for effectiveness in this field. Quantitative outcome assessment tools are needed to further supplement and enhance the credibility of the evidence. Surface electromyography (sEMG) is a technique for recording the bioelectrical signals of the neuromuscular system during muscle activity. It can quantify muscle activation patterns, fatigue levels, and neuromuscular coordination. Due to its specificity and sensitivity to muscle functional status, it has important application value in the quantitative assessment of upper limb functional recovery after stroke (13–15). Crucially, sEMG is easy to operate, non-invasive, and well-accepted by patients (14). However, few acupuncture studies have combined validated subjective assessment tools with sEMG to evaluate the efficacy of acupuncture in treating upper limb dysfunction following a stroke. In addition, the “placebo effect” in acupuncture clinical trials has always been a focus of attention, and there are still doubts about whether sham needle devices can effectively exclude nonspecific effects (16). Some sham acupuncture devices also omit tactile simulation, limiting the effectiveness of blinding in acupuncture trials.

To sum up, this study intends to conduct a single-center, primary investigator-blinded randomized controlled trial (RCT), combining validated scales for assessing upper limb motor function with objective surface electromyography indicators, aiming to evaluate the clinical efficacy of acupuncture treatment for upper limb dysfunction and to explore the neuromuscular driving mechanism of acupuncture in treating upper limb dysfunction after ischemic stroke. At the same time, a novel sham needle device will be used as the control group to provide high-quality evidence-based data to exclude the nonspecific effects of acupuncture.

## Methods

2

### Trial design

2.1

This study plans to conduct a single-center, investigator-blinded randomized controlled trial (RCT). By setting up the acupuncture (MA) group and sham acupuncture (SA) group for comparison, it aims to explore the efficacy and safety of acupuncture treatment for upper limb dysfunction in patients with ischemic stroke. Assessment scales related to upper limb function combined with surface electromyography (sEMG) will be used to comprehensively reflect the efficacy of acupuncture and its potential mechanisms. The study will randomly assign patients into two groups at a 1:1 ratio, with 37 cases in each group, recruiting a total of 74 patients.

The subjects will be hospitalized in the Rehabilitation Department of the Guangzhou University of Traditional Chinese Medicine Shenzhen Hospital (Futian). This study has been registered in the international traditional medicine clinical trial, and the details of the trial protocol and statistical analysis plan are available (Registration No. ITMCTR2025000228). This scheme is designed according to the SPIRIT declaration and reported according to the CONSORT 2025 as shown in Figure 1 (17). The schedule of enrolment, interventions, assessments, and visits to the participants is presented in Table 1, which also presents a schematic of the study design.

**Figure 1 fig1:**
[figure not shown]
Participants flow chart. CONSORT 2025 Flow charts: Flow charts of the two groups at each stage of the trial (e.g., recruitment, intervention allocation, follow-up, and data analysis). Acu, Manual-Acupuncture; Sham Acu, Sham-Acupuncture.

**Table 1 tab1:** Study design.

	STUDY PERIOD						
		Allocation	Treatment				Follow-up
TIMEPOINT**	*-t_1_*	0	*t_1_*	*t_2_*	*t_3_*	*t_4_*	*t_5_*
		Baseline	Week1	Week2	Week3	Week4	3-months
ENROLMENT							
Eligibility screen	X						
Informed consent	X						
NIHSS	X						
Demographic information	X						
Random Allocation		X					
INTERVENTIONS:							
MA							
SA							
ASSESSMENTS:							
FMA		X		X		X	X
MSS		X		X		X	X
ARAT		X		X		X	X
MAS		X		X		X	X
SAS		X		X		X	X
SDS		X		X		X	X
sEMG		X				X	
Biochemical indicators		X				X	
Blinding Index		X				X	
Adverse events			X	X	X	X	X

Study schedule of enrollment, interventions, and assessments. The template is from the SPIRIT 2013 statement. HA, hand acupuncture; SA, shame acupuncture; FMA-UE, Fugl-Meyer assessment upper extremity; MSS, Motor Status Scale; ARAT, Action Research Arm Test; MAS, modified Ashworth scale; SAS, Self-Rating Anxiety Scale; SDS, Self-Rating Depression Scale.

### Eligibility criteria

2.2

#### Inclusion criteria

2.2.1

The Diagnostic Points of Various Major cerebrovascular diseases in China in 2019 were formulated as per the Branch of Neurology of the Chinese Medical Association (18). The following patients will be included:

(1) They meet the above diagnostic criteria for ischemic stroke.(2) Aged between 35 and 80 years, sex is not limited.(3) 2 weeks to 6 months have passed following the first stroke.(4) Objectively measured upper limb dysfunction; National Institutes of Health Stroke Scale (NIHSS) score ≥ 5.(5) Conscious and stable vital signs.(6) Provide signed informed consent.

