### Randomization and allocation concealment

2.3

In this study, a centralized randomization system developed by the research team randomly assigned patients to the acupuncture and sham acupuncture groups in a 1:1 ratio. The module size was set to 4, and 37 patients were randomly assigned to each group. All assignment information was unpredictable and invisible until participant inclusion, and the assignment sequences were directly notified to the acupuncturist by the system to ensure fairness of the assignment sequence hiding and randomization process. After the investigator confirms the qualified cases, a third party submits the application to the central randomization system, which automatically assigns the group information according to the randomization method and sends the group information to the investigator and acupuncturist.

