### Sample size

2.5

The sample size calculation for this study was based on the primary outcome measure, the FMA-UE score. According to preliminary pilot results, the mean difference (MD) in FMA-UE scores between the acupuncture and control group after treatment was 11.5, with a standard deviation (SD) of 10.4. Meanwhile, the minimal clinically important difference (MCID) for the Chinese version of the FMA-UE is 4.6. This study was a superiority design, using PASS 15.0 software for sample size estimation. An independent samples t-test was employed, with a significance level set at *α* = 0.05 and power *β* = 0.8. It is estimated that the acupuncture group must reach the MCID value compared to the sham acupuncture group to be clinically meaningful. Therefore, the superiority margin is set equal to the MCID value of 4.6. The minimum sample size calculated is 58 cases. Considering a 20% dropout rate, the final sample size was determined to be 74 cases (37 cases each in the MA and SA groups).

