### Data processing and statistical analysis

2.10

Data analysis was performed by qualified personnel not involved in the study using the Modified Intention-to-treat (mITT) principle. mITT was defined as participants who were randomized, received at least one treatment, and were statistically analyzed using the SPSS (IBM SPSS Statistics, Version 26.0) software. The significance level was set at 5%. Continuous variables that conform to the normal distribution are represented by mean ± standard deviation (x ± s), and non-normal continuous variables are represented by median and quartile [M (P25, P75)]. Categorical variables are expressed as frequency (percentage) using a chi-square or Fisher precision test. For primary and secondary outcomes, an independent sample T-test was used to compare groups if normal distribution and homogeneity of variance were met; otherwise, the Mann–Whitney *U* test was used. Intragroup comparisons were performed using the paired sample T-test. According to missing outcome data, the last observation carried forward (LOCF) method or multiple interpolation was used to fill in the missing values. In addition, sensitivity analyses were performed to clarify the robustness of the results by comparing the conforming protocol analysis set (PPS) analysis with the ITT analysis set. The data obtained by sEMG were analyzed with the main outcome, FMA-UE, using Person/Spearman correlation analysis. Finally, we calculated the BI index to evaluate the success of blinded implementation.

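### Time since stroke, known at eligibility and ranging from 2 weeks to 6 months, is used neither in the stated allocation nor in the FMA-UE comparison, which costs precision

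*Protocol article*

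**What the plan says.** Section 2.2.1 (Inclusion criteria) of the protocol article admits patients when "2 weeks to 6 months have passed following the first stroke".

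Section 2.3 (Randomization and allocation concealment) describes a central system that "randomly assigned patients to the acupuncture and sham acupuncture groups in a 1:1 ratio" and adds: "The module size was set to 4, and 37 patients were randomly assigned to each group". It gives ratio, block size and concealment, and names no stratification or minimisation factor.

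Section 2.10 (Data processing and statistical analysis) says of the primary and secondary outcomes that "an independent sample T-test was used to compare groups if normal distribution and homogeneity of variance were met", with Mann-Whitney U as the fallback. Neither test takes a covariate. The section also says: "Intragroup comparisons were performed using the paired sample T-test".

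Section 2.5 (Sample size) rests on a pilot difference that "was 11.5, with a standard deviation (SD) of 10.4", and states that "the superiority margin is set equal to the MCID value of 4.6". The Limitations section does not mention the entry window.

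**The concern.** The outcome is a motor score followed over 4 weeks of treatment and to 3 months. A patient who enters at 2 weeks can plausibly be expected to improve more without needling than one who enters at 6 months. If so, time since stroke explains part of the spread in FMA-UE. With 37 patients per arm, chance can put noticeably more early entrants in one arm, and the stated analysis has no term to correct for that.

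Two things are at stake. Variance that a known covariate could explain stays in the error term. And once the baseline table is seen, an imbalance in time since stroke would leave the single unadjusted estimate open to challenge, with no pre-specified adjusted result to answer it.

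The paired within-group tests are a secondary matter. In patients who are still recovering, both arms can show significant change without any treatment effect, so these tests cannot speak to efficacy.

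**Working it through.** **Inputs from the document.** Entry window 2 weeks to 6 months (about 2 to 26 weeks; 26/2 = 13). Difference 11.5, SD 10.4, margin 4.6, alpha 0.05, power 0.80, minimum N 58, dropout 20%, final N 74.

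**Inputs that are assumptions.** The document gives neither a recovery gradient nor a distribution of entry times. Assume half the patients are early entrants (p = 0.5), who gain g points more than late entrants, with g from 2 to 10. Assume also that the SD of 10.4 comes from a similar mix of patients.

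**Step 1: the plan's own figure.** Net difference 11.5 − 4.6 = 6.9. One-sided 0.05: n = 2 × (1.645 + 0.842)² × 10.4² / 6.9² = 28.1, so 29 per arm and N = 58. With dropout, 29/0.8 = 36.25, so 37 per arm and N = 74. Both stated figures reproduce. (A two-sided 0.05 test would need 36 per arm before dropout.)

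**Step 2: existing standard error.** 10.4 × √(2/n) = 2.42 at 37 per arm and 2.73 at 29 per arm. The 95% half-widths are 4.7 and 5.4 points.

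**Step 3: how uneven the arms can be.** SD of the difference in early share = √(2 × 0.25/37) = 0.116. In simulation the difference reaches 15 percentage points or more in about 20% of trials, and 20 or more in about 8%.

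**Step 4: size of the shift and of the gain.** Shift at 95% = 1.96 × g × √(0.25 × 2/n). Variance share = 0.25 × g² / 10.4². Half-width after removing the time component = 4.74 × √(1 − share). Power = Φ(6.9 / [10.4 × √(1 − share) × √(2/29)] − 1.645), which is 0.81 unadjusted.

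| Gap g | Shift, 37 per arm | Shift, 29 per arm | Variance share | Half-width, 37 per arm | One-sided power, 29 per arm |
|---|---|---|---|---|---|
| 2 | ±0.46 | ±0.51 | 0.9% | 4.7 | 0.81 |
| 5 | ±1.14 | ±1.29 | 5.8% | 4.6 | 0.83 |
| 8 | ±1.82 | ±2.06 | 14.8% | 4.4 | 0.86 |
| 10 | ±2.28 | ±2.57 | 23.1% | 4.2 | 0.89 |

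In patient numbers, the gain is 1/(1 − 0.058) = 1.06 times at g = 5 and 1/(1 − 0.231) = 1.30 times at g = 10. A shift of 2 points needs g of about 7.8 (29 per arm) to 8.8 (37 per arm).

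**Step 5: a continuous alternative.** Let entry be uniform over 2 to 26 weeks and recovery exponential, with time constant 4 to 10 weeks and 10 to 30 points left to recover at onset. The SD of the 4-week gain is then 0.68 to 2.71 points. The shift, 1.96 × SD × √(2/n), is about ±0.3 to ±1.4 points.

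**Step 6: validity.** In 20,000 simulated trials with 37 per arm and an 8-point gap inside the SD of 10.4, the unadjusted two-sided t-test rejected in 5.2% under no effect.

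**Step 7: a trial that happens to be unbalanced.** With 29 per arm, a realised shift of 2 points against acupuncture lowers one-sided power from 0.81 to Φ((6.9 − 2)/2.73 − 1.645) = 0.56. A shift of 2 points in its favour raises the chance of falsely exceeding the margin from 0.05 to 1 − Φ(1.645 − 2/2.73) = 0.18. These figures are conditional on that imbalance; over all randomisations the error rate stays nominal.

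**The case against.** The strongest case against has four parts.

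- **The article is condensed.** It says that details of the protocol and analysis plan are available under the registration. Section 2.3 does not mention strata either way, so a reader should not infer that stratification has been ruled out. That stands. But section 2.10 is not silent: it names the between-group test, and that test takes no covariate. The point rests on this stated method.
- **Randomisation already handles natural recovery.** The concurrent sham arm removes it in expectation. That stands, and the simulation agrees. A reader might infer that the entry window biases the result; nothing in the documents supports that.
- **The size is assumed.** A reader might take about 2 points as the most the estimate can move. The documents contain no such figure. It is a 95% limit, not a maximum, and it needs a gap near 8 to 9 points; the continuous model stays at or below 1.4. Nor should the shift be added to the sampling error or read as bias against the 4.6-point margin: if the pilot mix was similar, the SD of 10.4 already contains it.
- **The paired tests are not called evidence of efficacy.** Section 2.10 gives the treatment comparison to the between-group test. That stands, so the remark on them concerns only how they are read.

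What remains is a prognostic variable, known for every patient, that the stated analysis leaves out.

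**Conclusion.** The point holds as a matter of efficiency, not validity. Entry spans 2 weeks to 6 months, no stratification factor is named, and the stated FMA-UE comparison is unadjusted. Under assumed gaps of 2 to 10 points, chance imbalance in time since stroke moves the estimated difference by about ±0.5 to ±2.6 points at 95%, and by as little as about ±0.3 under a continuous recovery model. This lies within the standard error of 2.4 to 2.7 points.

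The gain from using the variable ranges from negligible (gap 2) to a fall in the 95% half-width from 4.7 to about 4.2 points (gap 10). All of this depends on a recovery gradient that the documents do not give and on the pilot SD reflecting a similar mix of patients. The change is worth making because it costs almost nothing and settles in advance how an imbalance will be handled.

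**What to change.** In section 2.10, replace the unadjusted between-group test of FMA-UE with a pre-specified linear model (ANCOVA) containing treatment, baseline FMA-UE and time since stroke, for example as log days. Fix the form of the time term before unblinding. State that the within-group paired tests are descriptive only.

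The cost is one sentence and one variable that must be established for eligibility anyway; the model uses one further degree of freedom for time since stroke and one for baseline.

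If enrolment has not begun, stratifying the central randomisation by time since stroke is an optional addition; the model term alone gives most of the gain. Its downside is that incomplete last blocks may leave arm sizes slightly off 37/37. That is already possible, because 74/4 = 18.5 and the final block of 4 is incomplete as planned.

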#### Exclusion criteria

2.2.2

(1) Transient ischemic attack or reversible neurological impairment (RIND).(2) Neurological impairment is confirmed to be caused by brain tumors, brain trauma, brain parasitic disease, heart disease, or metabolic disorders, among others.(3) Severe spasticity of the upper limb.(4) Pregnant or lactating women.(5) Combined heart, liver, kidney, hematopoietic system, and endocrine system diseases or other serious primary diseases.(6) Patients with a history of psychiatric disorders or taking psychotropic drugs.(7) Other treatments that may influence the results of this study.

#### Withdrawal criteria

2.2.3

(1) Withdrawal as decided by the investigator:

① During the study, the participant has certain comorbidities, complications, or pathological changes that make it unsuitable to continue the study.② In the study, the participant has poor compliance, which may affect the evaluation of effectiveness and safety.③ The participant breaks the blindness or exposes the blinded data in an emergency.④ Adverse events and serious adverse events occurred, making a participant unsuitable to continue to receive the study.

(2) Withdrawal from the study.

According to the provisions of the informed consent, participants have the right to withdraw from the study midway, or the participants may not explicitly withdraw from the study, but may no longer receive medication and testing, and lose follow-up (which is also classified as a “withdrawal,” called “drop”). The reasons for withdrawal, such as poor efficacy, intolerance to certain adverse effects, inability to continue the clinical study, economic factors, and failure to explain the reasons for the loss of visits, should be understood as much as possible and recorded.

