#### Blinded index

2.7.4

Participants were asked to guess the type of acupuncture they received at the end of the acupuncture treatment. A third party recorded the data, and statisticians used the SAS macro %BBI2 for visual analysis to assess the success rate of blinding in the randomized controlled trial (29). The environment for this macro is based on SAS V.9.4 (SAS Institute, Cary, North Carolina, United States). For each group (e.g., MA and SA), the BBI is calculated as:

$${\mathrm{BBI}}_{n}=(2•T_{n}^{2}-1)•(\frac{N_{n,\text{correct}}+N_{n,\text{wrong}}}{N_{n,\text{total}}})$$

$$T_{n}^{2}=\frac{N_{n,\text{correct}}}{N_{n,\text{correct}}+N_{n,\text{wrong}}}$$

$$N_{n,\text{total}}=N_{n,\text{correct}}+N_{n,\text{wrong}}+N_{n,\text{unknown}.}$$

BBI ∈ [−1, 1], with 0 indicating a random guess; BBI ∈ [−0.2, 0.2] indicates a successful blinding.

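### Investigator withdrawal for poor compliance or a broken blind reads as leaving the study, so FMA-UE values that could be observed are imputed and some blinding guesses are never taken

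*Protocol article*

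**What the plan says.** Section 2.2.3 has two parts. The first is headed "Withdrawal as decided by the investigator" and gives four grounds. Ground 2 is that "the participant has poor compliance, which may affect the evaluation of effectiveness and safety". Ground 3 is "The participant breaks the blindness or exposes the blinded data in an emergency". Ground 1 covers comorbidities, complications or "pathological changes that make it unsuitable to continue the study", and ground 4 covers adverse events in similar terms. The second part deals with participants who leave of their own accord or are lost.

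Section 2.10 sets the analysis population: "mITT was defined as participants who were randomized, received at least one treatment". For missing outcomes, "the last observation carried forward (LOCF) method or multiple interpolation was used to fill in the missing values". The sensitivity analysis compares the PPS with the ITT set.

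Section 2.7.4 fixes the timing of the blinding question: "Participants were asked to guess the type of acupuncture they received at the end of the acupuncture treatment". An index between −0.2 and 0.2 counts as successful blinding. Table 1 marks the Blinding Index at baseline and week 4, and FMA-UE at baseline, week 2, week 4 and 3 months.

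**The concern.** Poor compliance and a broken blind both arise after randomisation, and neither prevents a score from being measured. If they end participation, the trial itself creates missing data in people who may be available and willing to be assessed. The mITT principle of section 2.10 then rests on filled-in values for exactly those participants.

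The loss need not be balanced. Section 2.6.1 describes needles inserted 10–30 mm, with participants asked about the qi sensation. Section 2.6.2 describes a blunt needle that neither penetrates nor produces that sensation. Recognising the allocation, or losing interest in attending, could plausibly differ between these experiences. Section 2.3 also has group information sent to the investigator, whereas section 2.4 says the primary researchers do not know it. The person who decides on withdrawal may therefore hold the allocation.

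Two results are at stake: the FMA-UE comparison, and the blinding index, which supports the stated aim of excluding nonspecific effects with a new sham device.

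**Working it through.** **1. Does withdrawal end assessment?** Ground 1 speaks of not continuing the study. Nothing in section 2.2.3 provides for outcome visits after withdrawal. Section 2.8.1 follows a participant after an adverse event only until the condition stabilises. Leaving the study is the natural reading, although the wording is loose.

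**2. What happens to FMA-UE?** A participant withdrawn in week 1 has only a baseline score to carry forward; one withdrawn in week 3 has the week-2 score. Both stay in mITT. A PPS would ordinarily exclude the same people, and the ITT set would use the same filled-in values, so comparing the two sets does not recover what was not measured.

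**3. Planned loss.** Section 2.5 assumes a difference of 11.5, SD 10.4 and margin 4.6, so the working difference is 11.5 − 4.6 = 6.9. With one-sided alpha 0.05 and power 0.8 this gives 29 per arm, or 58, as stated (sidedness is not given; one-sided reproduces the figure). Then 58/0.8 = 72.5, so 73, or 74 for equal arms. The allowance per arm is 0.2 × 37 = 7.4 for all causes together.

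**4. Size of a shift in FMA-UE.** If k of 37 in one arm have filled-in values that are off by e points on average, that arm's mean moves by k × e/37. The article gives neither k nor e. Taking e = 5 as an assumption, with loss in one arm only:
- k = 2: 2 × 5/37 = 0.27 points
- k = 4: 4 × 5/37 = 0.54 points
- k = 7: 7 × 5/37 = 0.95 points

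If patients are still improving, LOCF understates the arm that loses more. More loss in sham would inflate the difference, and more loss in acupuncture would shrink it.

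**5. Blinding index.** The formula in section 2.7.4 multiplies (2 × proportion correct among those who guess − 1) by (correct + wrong)/total. This simplifies to (correct − wrong)/total. Someone whose blind is broken would guess correctly. Removing k such people from an arm of 37 gives (correct − wrong − k)/(37 − k), which is lower than before, and closer to 0 as long as it stays positive. All counts below are assumptions.

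| Correct/wrong/unknown | None removed | 2 removed | 4 removed | 6 removed |
|---|---|---|---|---|
| 20/10/7 | 10/37 = 0.27 | 8/35 = 0.23 | 6/33 = 0.18 | 4/31 = 0.13 |
| 18/9/10 | 9/37 = 0.24 | 7/35 = 0.20 | 5/33 = 0.15 | 3/31 = 0.10 |
| 22/9/6 | 13/37 = 0.35 | 11/35 = 0.31 | 9/33 = 0.27 | 7/31 = 0.23 |

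In the first two rows a failing index comes inside the band. In the third it does not with up to six removals.

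**The case against.** Ground 3 may mean only a formal code break in an emergency, which would be rare. Suspecting one's allocation is not plainly the same as breaking the blind, and no procedure detects correct guessers during treatment. This stands, and it limits the effect on the blinding index. It does not touch ground 2, which has no such restriction.

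Grounds 2 and 3 do not themselves say that assessment stops, and an article may leave such detail to a full protocol. This stands in part. What is at issue is a stated rule whose neighbouring wording points to leaving the study. If only stopping treatment was meant, one sentence settles the outcome part; the timing of the guess still needs attention for anyone who discontinues early.

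The plan keeps these participants in mITT, imputes, and runs a sensitivity analysis. It does not drop them from the efficacy analysis, but imputation is a weaker answer than measurement.

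A reader might infer that outcomes are lost selectively by arm and that the mITT estimate is therefore biased. The documents give no rates by arm, and patients are hospitalised, which may limit non-compliance during treatment. A reader might also infer that the index will look successful because its failures are removed first. An example for that would be eight unblinded sham patients withdrawn while the other 29 have an index of 0, against 8/37 = 0.22 if all were counted. But eight exceeds the arm's whole allowance of 7.4, and seven would give 7/37 = 0.19, inside the band.

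**Conclusion.** The point holds as a badly fixed rule. As worded, sections 2.2.3 and 2.10 together replace observable FMA-UE scores with filled-in ones after two events that could plausibly depend on the arm. The size and direction of any bias are unknown. Under the assumption of 5 points per affected patient and loss in one arm only, the shift stays below 1 point for up to seven patients, against a margin of 4.6.

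The effect on the blinding index has a known direction, downward, but its size depends on counts that the documents do not give. It may be small if ground 3 covers emergencies only. The baseline entry for the index in Table 1 does not help, because a guess before treatment cannot register unblinding during treatment. Neither biased efficacy results nor a falsely reassuring index is demonstrated. The required sample size is unaffected.

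**What to change.** State in section 2.2.3 that grounds 2 and 3 are recorded as protocol deviations, used to define the PPS, and do not end outcome assessment. Continue FMA-UE and the other scheduled assessments to 3 months unless the participant withdraws consent, and analyse the observed values in mITT. In section 2.7.4, collect the blinding guess at any discontinuation as well as at the end of treatment, and include those answers in the index. Grounds 1 and 4 and all decisions on stopping treatment are left as they are.

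The cost is a short amendment and a few more assessments at visits that are already scheduled. Including non-compliers' observed values may dilute the estimate slightly.
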